**2.9.4 The secondary outcome of drug resistance among cases of active TB**

All positive mycobacterial cultures from subjects who develop active TB within 28 months post randomization will be sent to reference TB laboratories for identification and drug susceptibility testing. All international sites have access to reference TB laboratories, which participate in external quality control programmes with WHO supra-national reference laboratories.

**2.10 Measuring health system costs**

We will gather information on all health services (visits, consults, tests, drugs) used by participants’ during treatment, and if they develop active TB, as an integral part of the local and web-based data-bases. Hence this information will be routinely gathered as part of the trial, as was done in Phase 2. Investigators at each site will provide site specific estimates for values (costs) for all these health services, using methods that we have used in earlier studies 54, 171-173. (Details in RCT Appendix 4).

**2.11 Sample size requirements**

Our primary objective is to test whether 4RIF has superior effectiveness compared to 9INH in reducing occurrence of confirmed active TB, based on a planned intention to treat analysis. The number required depends upon the estimated rate of active TB in treated, and untreated patients, and the expected completion rates with 9INH. The expected rate of TB is hard to predict, since we will enrol patients at a wide range of increased risk. In the international sites, where most patients will be contacts (risk over 2 years of 3% 62 174 up to 8-10% 63, 175), or HIV infected (**annual** risk 3-8% 20, 21), cumulative incidence if untreated (or non-compliant) should exceed 5%, but may be only 2% in untreated subjects in Canada. Hence we assume an average cumulative incidence of 3% among untreated. Based on the assumption that 9INH has 90% efficacy if completed 140, but only 50% completion rate 70, 93, 96-102, and 4IRF efficacy is 90% the required sample size, calculated using Poisson distribution, would be 2,898 participants with full follow-up in each group (see Table S1 below). If re-calculated using the binomial distribution (and [*http://stat.ubc.ca/~rollin/stats/ssize/b2.html*](http://stat.ubc.ca/~rollin/stats/ssize/b2.html)) the sample size required would be 2% to 5% larger. Smaller differences in completion will reduce power, but higher event rates (that are certainly plausible) will substantially increase power.

**Table S1: Sample size required to detect superior effectiveness of 4RIF compared to 9INH**

*(calculated using Poisson distribution 176, assuming alpha=0.05 and two-sided tests)*

| **Expected cumulative incidence of TB**  **over 28 months after randomization** | | | **N (per group) to detect difference,**  **with power of:** | | |
| --- | --- | --- | --- | --- | --- |
| **No therapy** | **9INH**  (Completion 55%, Effectiveness 49.5%) | **4RIF**  (Completion 80%, Effectiveness 72%) | **60%** | **70%** | **80%** |
| 3% | 1.49% | 0.84% | 2,648 | 3,337 | 4,243 |
| 4% | 1.98% | 1.12% | 2,013 | 2,537 | 3,226 |
| 5% | 2.48% | 1.4% | 1,598 | 2,013 | 2,560 |
| **No therapy** | **9INH**  (Completion 50%, Effectiveness 45%) | **4RIF**  (Completion 80%, Effectiveness 72%) | **60%** | **70%** | **80%** |
| 3% | 1.65% | 0.84% | 1,809 | 2,279 | 2,898 |
| 4% | 2.20% | 1.12% | 1,357 | 1,709 | 2,173 |
| 5% | 2.75% | 1.40% | 1,086 | 1,368 | 1,739 |

Members of the same household will be randomized to the same regimen. When cluster randomization is used, sample size must be adjusted accordingly because members of the same cluster are no longer independent observations 177. Usually, the required sample size is inflated by a factor of *1+(m–1)*ICC*; where *m* is the average cluster size and *ICC* is the intra-cluster correlation coefficient which denotes how similar subjects from the same cluster are with respect to their risk of developing the outcome, compared to those in other clusters 178. Given that the cluster sizes will vary (in Phase 2, 20% of subjects were household contacts, of whom 60% were single contacts, and 40%, or 8% of all participants, were in groups of 2-4 persons - with an average number of 2.5 contacts), we adjusted for this via the method described in 178. This calculates the design effect as**: *1+[(cv2+1)m-1]*ICC*** where ***cv*** is a ratio of the standard deviation of the cluster sizes, ***m*** and ***ICC*** as before. Even assuming an ICC as large as 0.1 (ICC is typically 0.05-0.12 for spouse pairs 179), this only results in a design effect of 1.03 - meaning a 3% increase to 2985 per group. Allowing for 10% loss to follow-up the number must be increased to 3283 per arm. Patients will continue to be followed even if they stop therapy themselves (i.e. non-compliance), or their physician stops therapy (e.g. pregnancy or adverse events). Because 847 subjects, enrolled in Phase 2 of this trial, are still being followed for occurrence of active TB using the same methods as proposed here, the total of number of new participants required in this phase can be reduced to 5720.

We have assumed 4RIF efficacy of 90%, based on available evidence. As shown below, if 50% of the 2,898 randomized to each group complete therapy and 28 months follow-up, this would provide more than 90% power, to confirm **non-inferior** efficacy of 4RIF, if the **non-inferiority** margin was 25% - equivalent to a minimum efficacy of 4RIF of 65%. (In other words, we would declare 4RIF **non-inferior** to 9INH if the efficacy of 4RIF was not more than 25% worse than 9INH.) This efficacy has been considered sufficient for authoritative recommendations of 6INH 107, 138, which has had efficacy of 40-69% in trials 33, 61, 65, 68, 104, 128.

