**2.5 Inclusion and exclusion criteria**

**2.5.1 Inclusion criteria**

Adults (age > 18) with documented positive TST as defined below and prescribed 9INH for LTBI, following authoritative recommendations 107, 138:

**Note:** In the absence of a TST test, a positive QFT (or T-Spot) (according to manufacturers recommendations) (see screening, recruitment and randomisation procedures) is equivalent to a TST of 10 mm.

1. HIV positive , OR to start TNFa inhibitors, OR on transplant anti-rejection medications.(TST ≥5 mm or QFT +)

1. Close contact: >4 hours contact per week, for > 1 week with person with active pulmonary TB. (TST >5 mm or QFT +)
2. Apical/upper lobe fibronodular disease with area >2cm2 (shown in RCT Quick Guide) (TST >5 mmor QFT +)
3. Documented tuberculin conversion within two years. (Increase ≥ 6 mm, with subsequent TST >10 mm or QFT +)
4. Diabetes, renal failure, or immuno-compromised from medical condition or therapy (TST >10 mm or QFT +)
5. Casual contact: contact of <4 hours/week, with a person with smear positive pulmonary TB. (TST >10 mm or QFT +)
6. Tuberculin conversion within 2-5 years. (Increase of 10 mm or more with subsequent TST >10 mm or QFT +)
7. Have (1) **TWO** of the following  **four** factors if TST = 10-14mm or QFT +,

**OR** (2) **ONE** factor if TST >15mm:

- 1. Arrival in Canada, Australia, or Saudi Arabia in the past 2 years from countries with WHO estimated incidence greater than 100 per 100,000 (these are listed in the RCT Procedure guide - Appendix 5)
  2. BMI <19 (BMI calculations, see RCT Procedure guide);
  3. Any abnormality on chest x-ray compatible with past-TB infection e.g. calcified granuloma, or hilar lymph nodes, costo-phrenic angle blunting - other than fibronodular disease above.
  4. Cigarette smoking (at least a half pack per day) currently.

In the low and middle-income countries, LTBI therapy will usually be offered only to patients in categories 1& 2158, because of resource limitations, resulting in substantial differences in risk of active TB among untreated patients at the different sites. Balanced allocation of risk groups to the two study arms will be maintained by site-stratified randomization.

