At the Canadian sites, we anticipate 455 subjects enrolled annually, based on an expectation of similar enrolment at continuing sites, and the addition of Vancouver. The Vancouver site is the largest TB clinic in Canada with more than 800 persons treated for LTBI annually. Given the allocation of the same budget as for Montreal and with 33% more patients, it seems realistic to expect similar recruitment rates as in Montreal. We plan to double the capacity in Brazil by doubling staff and doubling the number of clinics at which patients will be enrolled. We anticipate little change in enrolment in Saudi Arabia. Two new sites will be added in West Africa; both have substantial experience and infrastructure for the conduct of randomized trials of active TB. We anticipate a rapid start-up with an average of 500 enrolments annually from both sites (letter from [name] - Appendix 1). In Seoul, Korea four University hospitals and the very busy clinic at the Korean Institute of TB (KIT) will be added, under the direction of [name] (Director of KIT - see letter in Appendix 1). Investigators at KIT were recently awarded a major grant for a 10 year longitudinal study of 3,000 close contacts. It is anticipated that at least 500 contacts with LTBI will be recruited annually at this site. In Australia and Saudi Arabia, the patient volumes are much lower, but addition of these two sites will be valuable because of the high quality TB programmes, and potentially greater generalizability of results to a broader range of settings. In addition both sites will cover all local costs – hence only travel costs for meetings, training, and supervision will be needed (see letters from [name], and [name] - Appendix 1). [name] will spend three months during years 1 and 2 in getting the study initiated at all these sites. (This plan is supported by his department Chair - see [name] letter in Appendix 1). If all sites enrol a total of 1,950 participants annually (see section 2.15), we should complete enrolment within 3 years, although we have planned recruitment over 3.5 years. And, as in Phase 2, enrolment will be monitored closely, and corrective actions taken promptly - including addition of sub-sites, and, if necessary, shifting operating budgets from under-performing sites.

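### The household design effect of 1.03 in section 2.11 does not follow from the stated formula and inputs, which give 1.013–1.014; the slip is conservative, but the inputs are Phase 2's and are carried unadjusted into Phase 3

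*Protocol*

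**What the plan says.** Section 2.11 first derives an unclustered size under Table S1 ("assuming alpha=0.05 and two-sided tests"). It states that the number needed "would be 2,898 participants with full follow-up in each group", for 1.65% on 9INH against 0.84% on 4RIF at 80% power.

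Below Table S1 it says that members of one household receive the same regimen. It gives the design effect for unequal clusters as 1 + [(cv² + 1)m − 1] × ICC, with m the mean cluster size and cv the variation in cluster size. The household inputs come from Phase 2: 20% of subjects were household contacts, 60% of them single, and the remaining "40%, or 8% of all participants, were in groups of 2-4 persons - with an average number of 2.5 contacts". With an ICC of 0.1, the protocol concludes that "this only results in a design effect of 1.03 - meaning a 3% increase to 2985 per group". That figure leads to 3,283 per arm after loss to follow-up and to 5,720 new participants after crediting the 847 from Phase 2.

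On the Phase 3 population:
- Section 2.11: "In the international sites, where most patients will be contacts". The sentence goes on to offer HIV infection as the alternative.
- Section 2.5.1, for low- and middle-income countries: "LTBI therapy will usually be offered only to patients in categories 1". The text continues to category 2; read in order, the first two entries are HIV or immunosuppressive therapy, and close contacts.
- Section 2.12, for Korea: "It is anticipated that at least 500 contacts with LTBI will be recruited annually at this site".

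No section gives an expected Phase 3 share or size of households with several participants.

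**The concern.** There are two distinct weaknesses. First, the factor of 1.03 cannot be recovered from the formula and figures beside it when the 8% is used as the text defines it, as a share of participants. The numbers 2,985, 3,283 and 5,720 all inherit the factor. Second, whatever its correct value for Phase 2, the protocol applies it to a trial with a different site mix without saying why the Phase 2 household pattern should hold.

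At stake are whether the sample-size paragraph can be reproduced and whether the stated 80% power is described accurately. The two weaknesses act in opposite directions: the arithmetic slip makes N slightly too large, and heavier household enrolment in Phase 3 would make it too small.

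**Working it through.** **Inputs (protocol section 2.11).** Rates 1.65% and 0.84%; two-sided alpha 0.05; 80% power; 8% of participants in groups of 2–4 with mean 2.5, the other 92% single; ICC 0.1.

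**1. Base size.** The square-root Poisson formula n = (1.960 + 0.842)² × 0.5 / (√0.0165 − √0.0084)² gives 2,898. It also returns 1,809 and 2,279 at 60% and 70% power, matching Table S1. The base size is sound, and 2,898 × 1.03 = 2,985 as printed.

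**2. Design effect as the text defines it.** Per 100 participants there are 92 singletons and 8/2.5 = 3.2 groups, so 95.2 clusters and m = 100/95.2 = 1.050. Sizes 2–4 with mean 2.5 give a mean squared group size between 6.5 (half 2s, half 3s) and 7 (three quarters 2s, one quarter 4s), so cv is 0.27–0.30. Because (cv² + 1)m is the mean squared cluster size divided by the mean, the formula reduces to

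1 + ICC × k × (1.6 to 1.8),

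where k is the share of participants in groups, 6.5/2.5 − 1 = 1.6 and 7/2.5 − 1 = 1.8. With k = 0.08 this is 1 + 0.1 × 0.08 × (1.6 to 1.8) = **1.013–1.014**. Reaching 1.03 with k = 0.08 would need an ICC of 0.03/0.144 to 0.03/0.128, about 0.21–0.23.

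**3. Probable source of 1.03.** Enter 92% and 8% as shares of clusters. Then m = 0.92 + 0.08 × 2.5 = 1.12, the mean squared size is 1.44–1.48, and the design effect is 1 + (1.44/1.12 − 1) × 0.1 to 1 + (1.48/1.12 − 1) × 0.1 = 1.029–1.032. That reading puts 0.20/1.12 = 17.9% of participants in groups, which contradicts the stated 8%.

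**4. Effect on N.**
- Per group: 2,898 × 1.0128 to 2,898 × 1.0144 = 2,935–2,940, about 1.5–1.7% below 2,985.
- Per arm, keeping the protocol's multiplication by 1.1: 3,229–3,234, against 3,283.

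**5. Power at 2,985 on the stated inputs.** Use Φ[(√0.0165 − √0.0084)/√(0.5/n) − 1.960] with n = 2,985 divided by the design effect. At 1.0128–1.0144 this gives 80.6–80.7%.

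**6. Sensitivity for Phase 3.** This is an assumption, because the protocol gives no Phase 3 household share. Group sizes are as in Phase 2, ICC is 0.1, and untreated incidence is held at 3%. The share k solves ICC × k × (1.6 to 1.8) = design effect − 1.

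| Design effect | Share of participants in groups (k) | Power at 2,985 |
|---|---|---|
| 1.013–1.014 | 8% | 80.6–80.7% |
| 1.03 | 17–19% | 80% |
| 1.05 | 28–31% | about 79% |
| 1.10 | 56–63% | about 77% |

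If every participant were a household contact and 40% of them were in groups, as in Phase 2, k would be 40%, the design effect 1.064–1.072 and power 78.4–78.7%.

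**The case against.** The strongest defence has four parts.

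- **The slip uses every stated input and errs on the safe side.** This stands. It is a weighting slip of about 1.5% in N, and power on the stated inputs is slightly above 80%. A reader might infer from a wrong factor that the design misses 80% power under its own assumptions. It does not.
- **The protocol does not say that most Phase 3 participants will be household contacts.** This also stands. A reader might infer that from the international site mix, but section 2.11 says contacts or HIV infected, and only Korea's 500 of 1,950 a year (26%) are explicitly contacts. Section 2.5.1 defines close contact by hours of exposure, not by shared residence. Under section 2.3.3, household members enrolled at a later date are randomized separately. Phase 2 already included Brazil and Saudi Arabia.
- **The same sites should have more events.** Section 2.11 expects untreated incidence above 5% at the international sites and perhaps 2% in Canada. Taking Korea, Brazil, Benin and Guinea (1,350 of 1,950, 69%) at 5% and the rest at 2% gives 0.69 × 5 + 0.31 × 2 = about 4.1%. Table S1 needs 2,173 per group at 4%; times 1.10 that is 2,390, well below 2,985. The losses in the last two rows of the table above therefore depend on holding incidence at 3%.
- **An ICC of 0.1 is within the range quoted.** Agreed. Using 0.12, the top of that range, moves the Phase 2 factor only to 1.015–1.017, so the choice is a matter of preference.

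What remains is that the printed factor contradicts its own inputs, and that those inputs are carried into Phase 3 without a stated assumption. Section 2.16 plans a GEE analysis for household clustering, which protects the inference but does not correct the sample-size paragraph.

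**Conclusion.** The point holds in limited form. On the formula and inputs in section 2.11, the design effect is 1.013–1.014, not 1.03, and the size per group is about 2,935–2,940, not 2,985. The direction is conservative. This result rests only on figures in the protocol and on group sizes of 2–4 averaging 2.5.

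The second part is a gap in justification, not a demonstrated shortfall. The Phase 2 household mix is used for a trial whose added sites are expected to enrol mainly contacts or HIV-infected patients, and 1.03 would be right only if about 17–19% of participants shared a household allocation. Power of about 79% at a design effect of 1.05 and 77% at 1.10 assumes 3% untreated incidence, Phase 2 group sizes and ICC 0.1. The documents do not establish that Phase 3 will reach those design effects.

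**What to change.** In section 2.11:

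1. Recompute the design effect with participant-weighted cluster sizes and show m and cv, so that the figure can be reproduced.
2. State the assumed Phase 3 share of participants in multi-participant households, and their mean size, as a range. Say in one sentence how this relates to the Phase 2 figures.
3. Replace 1.03 and 2,985 with the resulting range, and carry it through to the figures now given as 3,283 and 5,720.
4. Keep enrolment as planned and restate the power it gives across that range. Note that higher untreated incidence at the contact-heavy sites would raise it.

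The cost is one rewritten paragraph. No extra participants are needed and the analysis does not change; the stated power becomes a short range around 80%.

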**SECTION 2 THE PROPOSED TRIAL**

**2.1 Study design**

We propose a multi-centre randomized 2-arm positive control open-label clinical trial. Patients prescribed standard therapy for LTBI (i.e. 9 months INH) will be approached to participate before they begin therapy. After providing informed consent, subjects will be registered using a web-based system, accessible at all times. This system will verify eligibility and perform immediate on-line randomization, using a computer generated random sequence, in equal numbers to 4RIF or 9INH - both daily and self administered. Randomization will be stratified by site and in blocks of variable length. The primary end-point will be the occurrence of microbiologically confirmed active TB. Secondary end-points include occurrence of confirmed and probable active TB, Grade 3 or 4 adverse events (SAE), drug resistant active TB, and health system costs. All primary outcomes will be reviewed by an independent 3-member clinical review panel, and all SAE will be reviewed by a different independent 3-member panel. Both panels will be blinded to the study drug, and patient identity.

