**2.14 Loss to follow-up**

Our ability to follow all participants successfully for 28 months after randomization will be crucial. Our objective is to have less than 10% drop-outs; higher rates would be of concern, given the anticipated rate of the primary outcome of less than 3%. Loss to follow-up was 17% in Phase 2, although over 97% of subjects had some follow-up (see RCT Appendix 1: Table 7). Based on experience gained in Phase 2, we will ask for home, work, and cellular telephone numbers, plus email addresses of the study participants, at the time of their enrolment. We will also ask for four other contacts – close friends, or relatives living in the same city, or same country, or relatives remaining in their home country for recently arrived immigrants. This approach has been successful, in another ongoing trial of LTBI therapy at the Montreal Chest Institute, in keeping losses to less than 5% of those randomized, during 33 months of follow-up. The initial consent will include subjects’ permission to verify their occurrence of active TB using local nominal TB reporting databases – for all sites, and provincial health administrative data-bases for Canadian sites. This will provide a mechanism (that we have used 181, 182) to verify occurrence of active TB passively, and assess under-estimation of the study outcome, due to mortality or migration.

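### Section 2.11 allows for 10% loss by multiplying by 1.10 instead of dividing by 0.90, and credits all 847 Phase 2 participants despite their reported 17% loss, so 5,720 new participants fall 1–2% short of its full-follow-up requirement

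*Protocol*

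**What the plan says.** Section 2.11 of the protocol sizes the superiority comparison on people with complete observation: the base number "would be 2,898 participants with full follow-up in each group". It comes from the 80% column of the 3% untreated-risk row of Table S1 (1.65% with 9INH, 0.84% with 4RIF), "assuming alpha=0.05 and two-sided tests". Allocation is "in equal numbers to 4RIF or 9INH" (section 2.1).

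The text after Table S1 takes three further steps:

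- Clustering by household: "this only results in a design effect of 1.03 - meaning a 3% increase to 2985 per group".
- Loss: "Allowing for 10% loss to follow-up the number must be increased to 3283 per arm".
- Phase 2 credit: because 847 Phase 2 participants are still under follow-up, "the total of number of new participants required in this phase can be reduced to 5720".

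Section 2.14 states: "Loss to follow-up was 17% in Phase 2". The same sentence adds that more than 97% had some follow-up. Section 2.14 also sets a target of under 10% loss for the new trial. Section 2.11 does not use the 17%.

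**The concern.** When a requirement is expressed as participants fully followed, an allowance for a loss fraction L divides that number by 1 − L. Multiplying by 1 + L always falls short, because the loss also applies to the people added. Here the multiplication was used.

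The Phase 2 credit adds to the gap in the same direction. Subtracting 847 whole participants from a total inflated for 10% loss treats that cohort as if it too would lose only 10%. The protocol's own figure for the cohort is 17%.

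At stake is the agreement between the headline enrolment figure of 5,720 and the 80% power that justifies it.

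**Working it through.** **Inputs.** Event risks 1.65% and 0.84%, two-sided alpha 0.05, 2,898 per group at 80% power (Table S1); design effect 1.03, planned loss 10%, 847 Phase 2 participants, 5,720 new participants (section 2.11); 17% Phase 2 loss (section 2.14).

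**1. Reproduce the base number.** The square-root Poisson formula is n = (z₀.₉₇₅ + z_power)² / [2(√p₁ − √p₂)²]. With √0.0165 − √0.0084 = 0.12845 − 0.09165 = 0.03680, it gives 1,809, 2,279 and 2,898 at 60%, 70% and 80% power. All three match the Table S1 row.

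**2. Reproduce the later steps.**
- 2,898 × 1.03 = 2,985
- 2,985 × 1.10 = 3,283.5, the stated 3,283
- 2 × 3,283 − 847 = 5,719, the stated 5,720

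The plan's route is therefore established: it multiplied by 1.10 and subtracted 847 in full.

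**3. Check against the requirement.**
- Per arm: 3,283 × 0.90 = 2,955, below 2,985.
- Correct inflation: 2,985 / 0.90 = 3,317, which is 34 more per arm (1.0%).
- Total required with full follow-up: 2 × 2,985 = 5,970.

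| Loss | Expected with full follow-up | Shortfall against 5,970 |
|---|---|---|
| 10% throughout | (5,720 + 847) × 0.90 = 5,910 | 60 (1.0%) |
| 10% in new participants, 17% in the 847 | 5,720 × 0.90 + 847 × 0.83 = 5,148 + 703 = 5,851 | 119 (2.0%) |

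**4. New participants needed.**
- 10% throughout: 2 × 3,317 − 847 = 5,787 (67 more than 5,720).
- Phase 2 credited at 17% loss: (5,970 − 703) / 0.90 = 5,852.2, so 5,853 (133 more, or 2.3%).

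**5. Power if lost participants contribute nothing.** With effective n per arm = total / (2 × 1.03), power = Φ[(√p₁ − √p₂)√(2n) − 1.96].
- 5,970: n = 2,898, power 80.0%
- 5,910: n = 2,869, power 79.6%
- 5,851: n = 2,840, power 79.2%
- Sensitivity scenario, 17% loss throughout: 6,567 × 0.83 = 5,451, n = 2,646, power 76.3%

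**6. Power if lost participants contribute half the 28 months on average (an assumption).**
- 10% loss in new participants, 17% in the 847: 5,720 × 0.95 + 847 × 0.915 = 6,209 full-follow-up equivalents, power 81.5%.
- 17% throughout: 6,567 × 0.915 = 6,009 equivalents, power 80.3%.

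**7. Break-even.** In the second row of the table, 572 + 144 = 716 participants are lost and the gap is 119. It closes if those lost average 119 / 716 = 17% of 28 months, about 4.7 months. With 17% loss throughout, 1,116 are lost and the gap is 5,970 − 5,451 = 519, so break-even is about 13 months.

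**The case against.** A reader might infer that the trial misses 80% power. The documents do not support that. Section 2.16 analyses events per patient-year with log follow-up time as an offset, specifically so that time before loss counts. Section 2.14 says over 97% of Phase 2 participants had some follow-up. Sections 2.9.1.3 and 2.14 add registry matching of all randomized participants, and administrative databases for those lost in Canada. Under half-period follow-up, power is above 80% in every scenario shown. This part of the objection stands: 79.6% and 79.2% are lower bounds.

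A reader might also infer that 10% loss is an unrealistic assumption for new participants and that power is really about 76%. Section 2.14 discloses the 17%, describes added retention measures and cites another trial of latent TB therapy with under 5% loss over 33 months. The 10% is argued, so 76% is only a scenario.

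The figure of 703 is an inference. Section 2.11 says the Phase 2 cohort is still being followed, so its final loss could be higher or lower than 17%.

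Finally, the effect is small beside other uncertainties the plan accepts. Section 2.11 says a binomial calculation would need 2% to 5% more, and in Table S1 55% instead of 50% completion of 9INH moves the number from 2,898 to 4,243. Projected recruitment of 1,950 a year over 3.5 years is 6,825, above each corrected figure.

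None of this removes the arithmetic point. Section 2.11 sizes on full follow-up, makes an explicit allowance for loss and computes it wrongly. It does not invoke partial follow-up to cover the difference.

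**Conclusion.** The point holds as a minor arithmetic error. The figure of 3,283 should be 3,317, and the full credit for 847 does not agree with the 17% loss in section 2.14. On the plan's full-follow-up basis the shortfall is 60 participants (1.0%) at 10% loss throughout, or 119 (2.0%) if 17% of the 847 are lost.

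The power figures of 79.6% and 79.2% rest on the base-case event risks, the 1.03 design effect and no contribution from anyone lost. The 5,851 and 5,853 also assume that 17% is the final Phase 2 loss. It is not shown that actual power falls below 80%, nor that the 10% assumption for new participants is wrong.

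**What to change.** In section 2.11, replace 3,283 per arm with 3,317 (2,985 / 0.90), and state what loss is assumed for the 847. Then do one of the following:

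- Restate the number of new participants: 5,787 at 10% loss throughout, or about 5,853 if Phase 2 is credited at 17% loss, with that rate labelled as an assumption.
- Keep 5,720 and restate the full-follow-up power as about 79%, as a lower bound, noting that the person-time analysis in section 2.16 recovers partial follow-up and may restore 80%.

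The 76% may be given only as a sensitivity scenario for 17% loss throughout with no partial follow-up counted.

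The second option costs wording only, with no extra enrolment and a slightly less favourable stated power. The first adds 67 or 133 participants, within projected recruitment.
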